#### *Acidil and Placebo Groups*

Subjects assigned to groups 1 and 3 will receive a low potency combination supplement known as Acidil (20), commonly sold over the counter at health food stores. Acidil contains four homeopathic medicines (*Abies nigra*, *Carbo vegetabilis*, *Nux vomica*, and *Robinia pseudoacacia*), each in a 4C potency ( $10^{-8}$  dilution from the original starting tincture). Each of these medications is plant derived, has indications for heartburn and/or dyspeptic symptoms in homeopathic materia medica, and is listed in the *Homoeopathic Pharmacopoeia of the United States*, the official compendium of homeopathic drugs that are licensed for sale in the United States (21, 22). In addition, we will be filing an IND with the FDA to use this supplement. While there are no previously published studies of Acidil in the peer-reviewed literature, our rationale for studying Acidil is that it is a popular over the counter product widely sold in the US, France (as *Gastrocynesine*), and several other European countries for heartburn and related symptoms. This study thus begins to address a practical question regarding a commonly used and available supplement.

Subjects assigned to groups 2 and 4 will receive placebo pills similar in taste, appearance, and packaging to Acidil. All subjects will receive the study medication in a double-blind fashion. All subjects will also receive rescue antacid (Gelusil: aluminum hydroxide, magnesium hydroxide, simethicone) to take for breakthrough symptoms.

In addition to receiving oral instructions for how to take the study medication, subjects will also be provided with written instructions for how to take the study medication and rescue antacid (Appendix C). In general, they will be advised to allow 2 tablets to dissolve under the tongue 3 times per day, 15 minutes prior to meals. In the event of the situations below, they will be advised the following:

- If they experience severe GERD-related symptoms despite taking the study medication, they should take the rescue antacid, Gelusil, for symptom relief and continue taking the study supplement as prescribed.
- If they experience an immediate and marked worsening of their symptoms, they should follow the above instructions. If their symptoms do not improve after 2 additional doses, they should stop taking the supplement and call the study center.

- If they experience an improvement in symptoms, they should continue taking the study supplement as prescribed.
- If they experience an initial improvement in symptoms and subsequent symptom worsening, they should decrease dosing frequency to once or twice daily. If symptoms further worsen, they should stop the supplement entirely and call the study center.
- Subjects will be counseled to call the study center if they have any questions about their symptoms or dosing of the supplement.

During the consent process, we will not inform study subjects of the name of the study supplement or that it is a homeopathic product. Acidil is widely available over the counter, inexpensive (less than \$10 for 60 tablets), and we are unable to obtain a placebo that is an exact match for the product. As such, it would be very easy for subjects to unblind themselves during the trial and invalidate the results of the study. Furthermore, it is likely that most of the lay public do not know exactly what homeopathy is, and if they were to read the word “homeopathy” or “Acidil” in the consent document, they would likely search the internet or seek out additional information after the first study visit. Beliefs and expectations are known to influence treatment responses, and we are interested in studying how the length of time and depth of questions asked during a physician interview affects patients’ beliefs about the effectiveness of a treatment. Given the controversy surrounding homeopathy and the variable quality of information on the internet, subjects’ beliefs about the treatment would likely change and could weaken the difference between the effect of the standard vs. expanded interviews. Finally, many people would argue that calling Acidil “homeopathy” is also deceptive as classical homeopathy relies on the prescription of a single homeopathic medicine at higher dilutions closer to, or beyond, Avogadro’s number. The product being studied contains a combination of homeopathic medicines at relatively low dilutions (i.e., more concentrated than typical homeopathic medicines), and thus is more like a supplement than traditional homeopathy. We believe that the way we have described this product in the consent (a combination of 4 plant-based products, each in a low dose) is the best way to describe the intervention while maintaining the validity of the study. After the exit interview subjects will be informed of the name of the study supplement (Appendix F). However, because of the need to maintain the study physician’s blinding, they will not be informed whether they received Acidil or placebo until after the trial is over via a letter (Appendix F).

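### Marked worsening that builds gradually, with no earlier improvement, triggers no required call or stop; secondarily, the dose-reduction rule is not said to override the instruction to continue

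*Protocol*

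**What the plan says.** The instructions are in Protocol section B3.A, under Acidil and Placebo Groups. The default dose is two tablets three times daily. The situational rules are:

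- **Severe symptoms despite treatment:** "they should take the rescue antacid, Gelusil, for symptom relief and continue taking the study supplement as prescribed".
- **Abrupt deterioration:** "If they experience an immediate and marked worsening of their symptoms, they should follow the above instructions". Then: "If their symptoms do not improve after 2 additional doses, they should stop taking the supplement and call the study center".
- **Improvement:** continue at the prescribed dose.
- **Improvement followed by worsening:** "If they experience an initial improvement in symptoms and subsequent symptom worsening, they should decrease dosing frequency to once or twice daily". Then: "If symptoms further worsen, they should stop the supplement entirely and call the study center".
- **General advice:** "Subjects will be counseled to call the study center if they have any questions about their symptoms or dosing of the supplement".

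No sentence ranks these rules. Subjects also receive a written instruction sheet (Appendix C), which is not available for review. The First Study Visit section adds one contact seven days after that visit, to check medication-taking, diary completion and marked adverse effects.

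**The concern.** A required call is the only route by which the site learns of a deterioration between scheduled contacts without relying on the subject's initiative. The rules tie it to speed of onset or to an earlier improvement, and not to how bad the symptoms have become. A subject who becomes markedly worse over several days, having never improved, is as unwell as one who worsens at once, yet is told only to use antacid and carry on. Safety is part of Aim 1, so a gap in how worsening reaches the site matters even in a small pilot.

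The second issue is consistency of dosing. The severe-symptom rule has no condition on earlier improvement, and the reduction rule has no limit on severity. A subject who improves and then becomes severe satisfies both, and their actions differ. The protocol treats worsening after improvement as a real possibility: it is the first potential risk listed in section B5.

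**Working it through.** No sample-size or power figure bears on this point. The check sets each symptom course against the triggers as written.

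| Symptom course | Rules met | Instructed action | Required call? |
|---|---|---|---|
| Immediate and marked worsening, no earlier improvement | Abrupt-deterioration rule | Antacid and continue; stop if no improvement after 2 more doses | Yes, at the stop |
| Improves, worsens, worsens further | Reduction rule | Reduce, then stop | Yes, at the stop |
| Gradual but marked worsening, no earlier improvement | Severe-symptom rule, once severe | Antacid and continue | No |
| Improves, then becomes severe | Severe-symptom rule and reduction rule | Continue as prescribed, and also reduce | Only on further worsening |

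The third row is the gap. The abrupt-deterioration rule fails because onset is not immediate. The reduction rule fails because there was no initial improvement. What remains is the advice to call with questions, which is discretionary, and the day-7 contact, which cannot detect worsening that begins after it.

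**Length of the gap for one subject.** The dose is 3 per day, 2 tablets each. Assume visit 2 falls on day 14 (the protocol says approximately two weeks) and worsening starts just after the day-7 contact.

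- Doses possible before visit 2 with no required call: 3 x 7 = 21, which is 21 x 2 = 42 tablets.
- For immediate marked worsening without improvement, the stop and call come after 2 further doses, which is 2 x 2 = 4 tablets.

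**Overlap in the fourth row.** Per day, continuing gives 3 x 2 = 6 tablets, twice daily gives 4 and once daily gives 2. Over any seven full days this is 42, 28 or 14 tablets. The difference between 42 and either lower figure belongs to the overlap. The difference between 28 and 14 does not: it comes from the reduction rule's own choice of two frequencies and would exist with no overlap.

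The protocol gives no rate for either course, so these per-subject figures cannot be turned into an expected effect on an arm or an outcome.

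**The case against.** The strongest reply is that the stop rules were built around reactions the protocol describes: a transient aggravation (section B2, Homeopathy) and worsening after improvement, or proving (section B5). Slow worsening without improvement looks like uncontrolled reflux, for which antacid is a reasonable response. The product is a 10^-8 dilution, the manufacturer reports no US adverse event reports over ten years, and treatment lasts about two weeks. Subjects may call or withdraw at any time. This is a good reason to keep the rating low and not to force a stop. It does not explain why the site need not be told of a marked and persistent deterioration.

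On the overlap, the course-specific rule naturally governs over the general one, and continuing as prescribed can be read to include a dose already reduced. Section B5 supports this by saying that the problem usually resolves with less frequent dosing or stopping. Appendix C may also settle it. These arguments largely stand. What is left is that subjects apply the rules at home and the text shown does not state the precedence.

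A reader might infer more than the protocol supports:

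- **That immediate worsening means an outright stop.** It does not. The subject first takes antacid and continues, and stops only if there is no improvement after two more doses.
- **That the two dosing rules cannot be reconciled.** They can, by the reading above; it is simply unstated.
- **That treatment comparisons are biased.** The rules are identical in both double-blind arms, the analysis is intent-to-treat, and the diary records the amount of study medication used.
- **That mean exposure in an arm falls by some definite amount.** Any such figure needs an assumed number of affected subjects and an assumed day of change, neither of which the protocol gives.

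**Conclusion.** The point holds as a minor patient-safety improvement. As written, gradual marked worsening without earlier improvement never reaches a required call or stop. The protocol's backstops soften this but do not close it. The unstated precedence between continuing and reducing is a secondary wording matter.

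The 21-dose figure is an upper bound for one subject and rests on a 14-day interval and onset just after the day-7 contact. The frequency of such courses, and the effect on dosing consistency, cannot be quantified from the protocol. The conclusion also assumes that Appendix C carries the same rules as the protocol body. If it already requires a call for any marked worsening and ranks the rules, only the protocol text needs aligning.

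**What to change.** In the instructions under Acidil and Placebo Groups, and in Appendix C if it has the same wording:

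1. Remove the onset condition from the call requirement. Any marked worsening, whatever its onset, that persists after antacid and two further doses of the study supplement requires a call to the study center. The decision to stop or reduce is made on that call. Keep the existing stop rule for immediate marked worsening.
2. State that after an initial improvement the dose-reduction rule overrides the instruction to continue as prescribed, with antacid still allowed. Name one reduced frequency, for example twice daily, in place of a choice between two.

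The day-7 contact needs no change: it already covers medication-taking and marked adverse effects. Nor is a new follow-up rule needed for subjects who stop, since the intent-to-treat analysis and the re-contact attempts after a missed visit already support their retention.

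The cost is a few reworded lines, a few more calls and possibly a few more stops. Sample size, randomization and analysis are unaffected.

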#### Second Study Visit (Time 2 - approximately 2 weeks after first visit):

Study diaries will be collected and subjects will provide a second blood specimen (if they consent to the repository study) and complete study questionnaires (medication and supplement use, GSRS, Nepean Dyspepsia Index, GERD-HRQL, SF-12, MYMOP, treatment satisfaction, credibility questionnaire, predicted treatment assignment, belief in homeopathy, see Table 1). Subjects will then have a brief semi-structured exit interview with the study physician or another member of the research team (Appendix D) inquiring about their use of the study medication, symptoms, and experience in the trial. After the interview, subjects will be debriefed regarding the concealment of the doctor-patient interaction study in this trial and will be informed of the name of the study supplement (Appendix F). The second study visit is anticipated to last approximately 1 hour. Subjects who continue to experience symptoms at the end of the trial will be referred to their PCP for further evaluation.

#### Testing and Outcome Measures:

All testing will be conducted at the BIDMC GCRC on east campus. A schedule of testing is outlined in the table below. All testing will be conducted by study staff and physicians who are blinded to treatment assignment (except for the study physician who will know whether the patient is receiving the standard or expanded interview).

| Study Measures and Timepoints                                                                                                                                                                                                           |                                                                       |                                                                                        |            |    |    |   |
|------------------------------------------------------------------------------------------------------------------------------------------------------------------------------------------------------------------------------------------------|-----------------------------------------------------------------------|----------------------------------------------------------------------------------------|------------|----|----|---|
| #                                                                                                                                                                                                                                              | Measure/Procedure                                                     | Description/Rationale                                                                  | 0          | 1a | 1b | 2 |
| 1                                                                                                                                                                                                                                              | Study Diary                                                           | Daily dairy assessing GERD, dyspeptic, & other symptoms and medication use             | Throughout |    |    |   |
| 2                                                                                                                                                                                                                                              | Anthropomorphic data                                                  | Height, weight, BMI                                                                    |            | X  |    |   |
| 3                                                                                                                                                                                                                                              | Demographic Questionnaire                                             | E.g., age, gender, race/ethnicity, smoking status, alcohol & caffeine use              |            | X  |    |   |
| 4                                                                                                                                                                                                                                              | Medication Questionnaire                                              | List of current medications & supplements                                              |            | X  |    | X |
| 5                                                                                                                                                                                                                                              | GSRS - Gastrointestinal Symptom Rating Scale (23)                     | 15 item measure of GI symptoms (5 subscales), validated in patients with GERD          |            | X  |    | X |
| 6                                                                                                                                                                                                                                              | GERD-HRQL (24)                                                        | 11 item measure of GERD HRQL                                                           |            | X  |    | X |
| 7                                                                                                                                                                                                                                              | Nepean Dyspepsia Index (25)                                           | 10 item measure of dyspepsia-specific HRQL                                             |            | X  |    | X |
| 8                                                                                                                                                                                                                                              | SF-12 (26)                                                            | 12 item HRQL instrument in 6 domains                                                   |            | X  |    | X |
| 9                                                                                                                                                                                                                                              | MYMOP – Measure Yourself Medical Outcome Profile (27)                 | 7 item measure of impact of treatment on main symptoms and overall well-being          |            | X  |    | X |
| 10                                                                                                                                                                                                                                             | Treatment satisfaction (28)                                           | 4 item measure for satisfaction with GERD treatment                                    |            |    |    | X |
| 11                                                                                                                                                                                                                                             | Borkovec & Nau Credibility Questionnaire (29)                         | 4 item measure of confidence in treatment efficacy                                     |            | X  | X  | X |
| 12                                                                                                                                                                                                                                             | CARE – Consultation and Relational Empathy (30)                       | 10 item measure of patient’s perception of empathy from the physician                  |            |    | X  |   |
| 13                                                                                                                                                                                                                                             | CAMBI - Complementary and Alternative Medicine Beliefs Inventory (31) | 17 item measure of beliefs about complementary and holistic health                     |            | X  |    |   |
| 14                                                                                                                                                                                                                                             | Treatment assignment                                                  | 2 questions about predicted treatment assignment and certainty                         |            |    |    | X |
| 15                                                                                                                                                                                                                                             | Belief in homeopathy                                                  | 2 questions about whether patient has heard about homeopathy and what they think of it |            |    |    | X |
| 16                                                                                                                                                                                                                                             | Interview                                                             | Semi-structured exit interview to assess experience with the trial                     |            |    |    | X |
| 0 = Telephone screening
1a = 1 st study visit, before the standard/expanded interview
1b = 1 st study visit, after the standard/expanded interview
2 = 2 nd study visit, 2 weeks later, end of study |                                                                       |                                                                                        |            |    |    |   |
| # Copies of all instruments are in Appendix D.                                                                                                                                                                                                 |                                                                       |                                                                                        |            |    |    |   |
| Primary Measures
Study diary: GERD and dyspepsia symptom frequency and severity will be assessed by reviewing daily                                                                                                           |                                                                       |                                                                                        |            |    |    |   |

study diaries similar to those used in prior trials of pharmaceuticals for GERD (28, 32-34). The study diary includes a 5 point scale assessing the severity of symptoms (daytime heartburn, nighttime heartburn, acid regurgitation, epigastric pain, fullness after eating, early satiety, flatulence, belching, and nausea). In addition, the study diary will assess the presence of any other non-GERD, non-dyspeptic symptoms and their severity, potential side effects, and the amount of study medication and rescue antacid used.

